**4.0 RESEARCH DESIGN**

**4.1 The Research Team**

The research team includes partners from universities, AIDS service organizations (ASOs), government, and the Poz Prevention Working Group (PPWG). The PPWG, the majority of its members who are themselves HIV+ MSM, has been working for more than a year on effective and sustainable HIV prevention for HIV+ MSM with the assistance of the AIDS Bureau of the Ontario Ministry of Health and Long Term Care. The partners bring expertise to the table in research, knowledge translation, intervention delivery, policy formulation and implementation, program evaluation, and multisectoral collaboration. Many of the members have been working together over a period of several years conducting applied research and collaborating on program and policy approaches to prevention, support and treatment related to HIV and AIDS. All of the team members were members of the team when the team was awarded a 1-year Ontario HIV Treatment Network Strategic Applied Research and Training (START) Development Grant in Prevention Research. This type of grant was awarded to multidisciplinary teams of community-based and/or academic researchers to develop community-based research in HIV prevention. For our team, the purpose of the START grant was to develop the infrastructure to design the present Phase II behavioural intervention trial to reduce HIV transmission risk behaviour among HIV+ MSM.

**4.2 Overview of the Study Design**

Written informed consent will be obtained prior to study enrolment including permission to complete study measures. Those who agree to enrol and meet inclusion criteria will be scheduled for a single assessment session to complete a demographics questionnaire, self-report measures, and a brief interview. Participants will complete 6 sessions of a small-group sexual health intervention to reduce sexual risk behaviour. Assessments will be conducted at the completion of each 6-session group, with follow-up assessments conducted at post-intervention and at 3 months following the end of each group.

**4.3 Sample**

Individuals will be eligible to participate in the intervention if they: (1) are HIV+ men who report UAI with a partner of HIV-negative or unknown HIV status in the past 3 months; (2) speak and understand English, (2) anticipate that they will be able to attend all workshops; and (3) are willing to participate in program monitoring and evaluation. Persons will be excluded if it is found that their ability to respond to study measures could be compromised by 1) central nervous system conditions (e.g., advanced HIV-associated dementia), 2) acute psychotic conditions, 3) acute mood dysregulation (e.g., manic states), and/or 4) debilitating physical conditions. For ethical reasons, all participants may withdraw from the research component of the study while still remaining in the intervention. Based on the literature, we anticipate that a number of participants will display psychological or other lifestyle characteristics that are strongly associated with sexual risk taking. They will be offered referral to counselling where appropriate; however, the decision to pursue such additional support will be left with the individual men and will not influence their eligibility to participate in the intervention. To avoid conflict of interest, participants who are given referrals will be referred to counselling with providers outside the study team. In addition, if a participant experiences distress at any time, referrals for counselling will be ready at hand. Intervention program facilitators will be trained in group facilitation and will be knowledgeable about referral sources for HIV+ group members who seek information or counselling, and the project will be housed at the AIDS Committee of Toronto which has HIV-related counselling and information resources.

**4.4 Sample Size Estimation**

For the quantitative data analyses, to examine changes in UAI with HIV-negative or unknown serostatus partners, random coefficient regression (also known as multilevel modeling) analyses will be conducted. The random regression model employs time as a within-subjects variable, and subject-specific intercepts and slopes for the time effect (i.e., trajectories) are summarized with mean and variance parameters. The analysis has several important advantages. It accounts for serial correlation within subjects, is relatively robust to randomly missing data, and can incorporate certain non-random missing data, especially those arising from drop-outs, without biasing model estimates. Following the approach for trajectory modeling outlined by Muthén & Muthén (2002), power analyses suggest an N=40 to detect a meaningful average change (i.e., medium effect size) in UAI with =.05, and 1-=.80. Given that the groups will have 6 persons each, with 7 groups, the final sample size will be N=42.

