There have been far fewer behavioural interventions specifically focusing on reducing HIV transmission risk behaviour among HIV+ MSM. The relative lack of behavioural interventions for HIV+ MSM is problematic because behavioural interventions including samples with more than 35% HIV+ MSM were not efficacious in a recent meta-analysis41. Another40 meta-analysis of the positive prevention literature reported that interventions were efficacious to the extent that they did not focus on HIV+ MSM. In one of the largest and most intensive interventions developed to date, the Seropositive Urban Men’s Intervention Trial (SUMIT) found that participants had less receptive UAI after the 6-week course, but the effect faded 3 months later50. The SUMIT investigators speculated that SUMIT’s lack of efficacy may have been due to the influence of some participants in small group discussions who “disclosed that they regularly had unprotected sex, that they believed that their partners should be responsible for their own health, and that they were not convinced that they could transmit HIV during receptive anal or insertive oral sex”. This is particularly noteworthy as these views are recognizable as central tenets of the bareback sub-group of MSM.

In summary, from previous intervention research and our own interviews with Toronto MSM having UAI most or all of the time6, it appears that it is necessary to engage the emerging culture of risky sex among HIV+ MSM if the incidence of UAI, especially with partners of negative or unknown serostatus, is to be reduced. The present study will address this challenge in Canada by engaging HIV+ MSM in a community setting and employing an empirically supported model, the Information-Motivation-Behavioral Skills51,52 focusing on information, motivation, and behaviour skills as a means to prevent HIV transmission risk behaviour. The IMB model will be delivered by motivational enhancement counseling (also known as “motivational interviewing”), a counseling technique that that expresses empathy for the participants, highlights differences between current behaviour and current health promotion goals, avoids argumentation with clients, and supports a participant’s self-confidence in his ability to engage in risk reduction behaviours53-56.

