**4.9.3 Quantitative Measures**

The quantitative measures used in this study have been demonstrated to possess good reliability and validity, as well as documented associations with risky sexual behaviour23,51,52,59,60. It is anticipated that the entire protocol will take approximately 50 minutes to complete at each timepoint: baseline, post-intervention, and 3 months after the end of the intervention.

**Demographics Questionnaire.** Participants will complete a demographics questionnaire assessing age, ethnic/racial background, religious affiliation, educational level, living situation, marital/partner status, socioeconomic status, and sexual orientation.

**Primary Endpoint Variable: Unprotected Sexual Behaviour.** Participants will be asked to indicate their frequency of unprotected anal intercourse with HIV-negative or unknown HIV status partners in the past 3 months.

**Secondary Endpoints.** Secondary endpoints will also examine protected and unprotected 1) insertive and receptive anal intercourse with men, 2) anal and/or intercourse with women with and without a condom in the previous 3 months with partners who were HIV+, partners who were HIV-negative, and partners of unknown serostatus. Second, participants will be asked to indicate their number of HIV+ partners, HIV-negative partners, and partners of unknown serostatus in the previous 3 months. Third, participants will be asked if they had insertive or receptive anal intercourse or vaginal intercourse with their last sex partner, as well as their last partner’s serostatus.

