**4.10.2 Research Stage II – Data Collection**

Data collection will begin in month 4 of Year 1 and will continue through month 6 of Year 2 of the study. Persons in the study who contact the study office will be informed about the opportunity to participate in the study while waiting for their appointments. Specifically, they will be told that the study is involves a series of workshops intended to improve sexual health among HIV+ MSM, that participation entails responding to several questionnaires and a brief interview at a baseline assessment taking about 120 minutes to complete, a series of 6 workshops of 90 minutes each, a post-intervention assessment of 60 minutes, and a 3-month follow-up of 120 minutes. They will also be told that $30 per hour will be provided in exchange for participation. [name] have found these recruitment procedures to be both unobtrusive and effective in other larger scale studies of HIV+ MSM.

Upon obtaining informed consent, quantitative measures will be administered in questionnaire format. Upon completion of the protocol, participants will be debriefed and given the opportunity to ask any questions. Participants will then be remunerated at $30 per hour. Qualitative interviews will explore in greater depth the evaluative questions in 4.9.2 above and also the degree to which the workshops resonated with participants’ everyday lives by asking about decision-making in recent sexual encounters.

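### A single slope over three visits gives the post-intervention visit little or no weight, so an early fall that partly fades would be attenuated

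*Protocol*

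**What the plan says.** Section 4.4 gives the quantitative analysis for unprotected anal intercourse (UAI) with HIV-negative or unknown-status partners, the primary endpoint in Section 4.9.3. "The random regression model employs time as a within-subjects variable". How change is then summarised follows in the same sentence of that section: "subject-specific intercepts and slopes for the time effect (i.e., trajectories) are summarized with mean and variance parameters". It does not use the word linear, fix how time is coded, or name a quadratic term, a visit factor or a contrast between visits.

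Section 4.9.3 measures the endpoint at "each timepoint: baseline, post-intervention, and 3 months after the end of the intervention", with a 3-month recall each time. Section 4.2 fixes the second gap: "follow-up assessments conducted at post-intervention and at 3 months following the end of each group". The first gap is not stated. Section 4.10.2 gives only "a series of 6 workshops of 90 minutes each", with no interval between sessions.

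Section 3.0 makes the effect size the aim of the trial, and Section 5.0 says it will feed the design of a randomized controlled trial. In Section 2.2 the protocol reports that in an earlier large trial in HIV-positive MSM "participants had less receptive UAI after the 6-week course, but the effect faded 3 months" later. The size of that fade is not given.

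**The concern.** The two follow-up visits fall at the two moments where the earlier trial saw different results: just after the course and 3 months on. A straight-line slope folds both into one number. It cannot show a drop followed by a partial return, and it draws almost nothing from the post-intervention visit. At stake is the main product of the trial. The later RCT would be planned from a rate of change that can understate the immediate effect and, depending on visit spacing, distort the 3-month effect as well.

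**Working it through.** **The plan's own figure.** Section 4.4 states N=40 for a medium effect, alpha 0.05 and power 0.80. Taking medium as d=0.5 on a paired change (an assumption), (1.960+0.842)²/0.5² = 31.4, so 32 by the normal approximation, or 34 by the t distribution; one-sided, 25 and 27. Forty appears only with an unstated input, such as 15% dropout (34/0.85 = 40) or 20% dropout (32/0.80 = 40). The growth-model parameters are not given, so N=40 can be neither reproduced nor refuted. The point below does not depend on it.

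**First gap.** The data collection statement reads: "Data collection will begin in month 4 of Year 1 and will continue through month 6 of Year 2". That is about 15 months. Less 3 months of follow-up, 12 months remain for 7 groups, or 52/7 = 7.4 weeks per group if they run one after another. This fits roughly weekly sessions (about 1.5 months) but does not prove them; sessions two weeks apart would make the two gaps about equal. Both cases are shown.

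**Slope weights.** With complete, balanced data and a random intercept and slope, the estimated mean slope equals the least-squares slope (checked numerically at 0, 1.5, 4.5 months). The weight of visit j is (t_j − mean t)/SS.

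- *0, 1.5, 4.5 months:* mean 2; deviations -2, -0.5, 2.5; SS = 4 + 0.25 + 6.25 = 10.5; weights -0.190, -0.048, +0.238 per month.
- *0, 2, 5 months:* weights -0.184, -0.026, +0.211.
- *0, 3, 6 months:* weights -0.167, 0, +0.167. Coding 0, 1, 2 also gives the middle visit weight 0.

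**Effect on the fitted change.** Let the true change be -D at post-intervention and -fD at 3 months, where f is the share retained. At 0, 1.5, 4.5 months the slope is 0.048D − 0.238fD. The fitted change is the slope times the months since baseline.

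| f | True change (post, 3 months) | Fitted, visits at 0, 1.5, 4.5 (post, 3 months) | Fitted, equal spacing (post, 3 months) |
|---|---|---|---|
| 0 | -D, 0 | +0.07D, +0.21D | 0, 0 |
| 0.2 | -D, -0.2D | 0, 0 | -0.10D, -0.20D |
| 0.5 | -D, -0.5D | -0.11D, -0.32D | -0.25D, -0.50D |
| 1 | -D, -D | -0.29D, -0.86D | -0.50D, -D |

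The sign turns where 0.048 = 0.238f, so f = 0.20; at 0, 2, 5 months it turns at f = 0.125. A fully sustained effect is 14% short at the last visit under 0, 1.5, 4.5 months and exact there under equal spacing.

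**Power at N=42.** Assumptions: D = 0.5 SD of change, two-sided 0.05, compound symmetry, no random-slope variance, no dropout; for the 2-df test of visit means, within-subject correlation 0.5.

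| f | Slope, 0, 1.5, 4.5 | Slope, equal spacing | 2-df visit test | Baseline-to-post contrast |
|---|---|---|---|---|
| 0 | 0.11 (estimate in the wrong direction) | 0.05 | 0.91 | 0.89 |
| 0.2 | 0.05 | 0.10 | 0.85 | 0.89 |
| 0.5 | 0.18 | 0.35 | 0.80 | 0.89 |
| 1 | 0.79 | 0.89 | 0.91 | 0.89 |

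**Recall window.** With a 1.5-month course, (3 − 1.5)/3 = half of the post-intervention recall predates baseline. An effect E held through the course and then fading linearly to zero over 3 months would be recorded as about 0, -0.5E, -0.5E, with slope -0.190 × 0.5E = -0.095E per month. The two follow-up visits therefore cover different mixtures of time.

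**The case against.** Four arguments on the other side carry weight.

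- **Form not fully fixed.** Section 4.4 is a sample-size section. It does not say linear, and time coding can be settled in a statistical analysis plan, which is not at hand. This stands as a limit. Still, a model described by intercepts and slopes, with no other term named, is most naturally read as a straight line.
- **Evidence for a fade.** The earlier trial's result concerns receptive UAI, not this endpoint. Section 2.4.1 says this intervention rests on a different implementation model. The fade is a pattern the protocol gives reason to expect, not a forecast.
- **Recall.** The 3-month window can turn a real fade into a record that looks sustained, and the slope then has the right sign. That weakens the extreme examples. It does not make one slope a good summary of visits that cover different periods.
- **The remedy has the same blind spot if used narrowly.** With visits coded 0, 1, 2 and complete data, testing the slope is the same as testing baseline to 3 months. Making that contrast primary would also show nothing after a full fade. This is correct, so both contrasts must be reported.

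A reader might infer that the planned model will return zero or worsening for a real effect. The documents do not support that: it needs a near-complete fade, no size of fade is given, and worsening also needs a first gap shorter than the second. Even with a full fade at 0, 1.5, 4.5 months, the chance of a significant slope is only 0.11. Nor do the documents show that the visits are unequally spaced, that a sustained effect is always understated at the last visit, or that N=40 or 42 is wrong.

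**Conclusion.** The point holds in limited form. Read as a straight line, the stated slope gives the post-intervention visit weight 0 (equal spacing) or -0.048 against -0.190 and +0.238 (0, 1.5, 4.5 months). If half the early fall is retained, the fitted fall at post-intervention is 0.11D to 0.25D against a true D, and power at N=42 is 0.18 to 0.35, against 0.89 for a direct baseline-to-post contrast. Above about 20% retained, the sign is right and the effect is attenuated. At the last visit, a sustained effect is understated (14%) only under the unequal spacing.

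This rests on the straight-line reading, the assumed first gap, d=0.5 and complete data. The arithmetic concerns means on a raw or log scale, not the dichotomized fallback in Section 4.10.3. The change is worth making because the effect size is the purpose of the trial and the remedy is cheap.

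**What to change.** In Section 4.4, replace the slope as the summary of change with time as three visit categories, preferably with unstructured within-subject covariance. Report two contrasts, baseline to post-intervention and baseline to 3 months, each as an effect size with a confidence interval. Name in advance which one defines the effect size for RCT planning. If it is the 3-month contrast, state that it measures the sustained effect and will not show an early effect that fades, so the post-intervention contrast stands beside it. State the planned interval between sessions, and note that with a short course the post-intervention recall overlaps the period before baseline.

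Cost: protocol wording and one extra fixed-effect parameter, with no new data. An unstructured covariance has 6 parameters (3 variances, 3 covariances), against 4 for a random intercept and slope (2 variances, 1 covariance, 1 residual variance). If change is truly linear, there is a small loss of efficiency.

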**2.4.2 Structure of the Intervention**

The intervention will take the form of a small counselling group, since this is one of the most common intervention forms for similar populations. Recent studies have found positive effects on cardiovascular health behaviours (e.g., exercise, diet) using motivational enhancement counselling in a small group-forma**t73.** Participants will be organized into 7 groups of approximately 6 participants, each of which will be led by 2 facilitators who are HIV+ MSM. Months 1-4 will be spent completing the final version of the intervention manual, based upon data that will be received through focus groups with HIV+ MSM and with prevention and care providers for HIV+ MSM. These data come from the preliminary one-year project received by our team and will be completely analyzed by March 2009 and ready for incorporation into the manual. Per the IMB theoretical model and the motivational enhancement counselling treatment model, an outline of this manual has already been created and is found in Appendix 1.

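### Section 4.4 sizes the study and specifies the model as if the 42 men were independent; if change is correlated within the seven treatment groups, the precision and the 80% power are overstated

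*Protocol*

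**What the plan says.** Section 4.4 plans a random coefficient regression in which "subject-specific intercepts and slopes for the time effect (i.e., trajectories) are summarized with mean and variance parameters". The only dependence it claims to handle is within person: "It accounts for serial correlation within subjects". Multilevel there means time points within a man, not men within a treatment group.

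The section then reports that "power analyses suggest an N=40 to detect a meaningful average change (i.e., medium effect size) in UAI with" a 5% significance level and 80% power. The next sentence brings in the groups: "Given that the groups will have 6 persons each, with 7 groups, the final sample size will be N=42". No ICC, design effect or group-level variance appears in the protocol.

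Section 2.4.2 sets out the delivery: "Participants will be organized into 7 groups of approximately 6 participants, each of which will be led by 2 facilitators who are HIV+ MSM". Section 2.4.1 says the small-group format is meant to foster social interaction, and describes a behavioural skills component that draws on what the group knows to help individual members change. Section 2.2 reports that the investigators of an earlier group trial in HIV+ MSM speculated that its lack of efficacy "may have been due to the influence of some participants in small group discussions", and the protocol calls this particularly noteworthy.

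**The concern.** Men treated together, who are meant to influence one another, may change together. If they do, 42 men carry less information about the mean change than 42 independent men. A model without a group term then gives a standard error that is too small, and a sample size derived under independence is too low for its stated power.

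This bears on the study's main purpose. Section 1.0 makes determining the effect size the primary objective, and section 5.0 says the estimate will be used to design a randomised trial. An interval that is too narrow would overstate how well that planning figure is known.

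**Working it through.** **Inputs.** From section 4.4: N=40 before rounding, final N=42 (7 × 6), significance level 0.05, power 0.80, a medium effect on average change. From section 2.4.2: seven groups of about six. Not in the protocol and therefore assumed: the ICC of the change (0.01 to 0.10), a two-sided test, no dropout, and the numerical effect size.

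**The plan's own figure.** N=40 can be neither confirmed nor refuted, because no effect size, variance or within-person correlation is given. A paired-change t-test with standardised change d=0.5 needs 34 men for 80% power. N=40 results if 0.5 is on the baseline SD scale with a pre-post correlation of about 0.40, since 0.5/√(2 × (1 − 0.40)) = 0.456. I therefore calibrate: the change effect that gives exactly 80% power at N=40 by the noncentral t is d=0.454. A second run uses d=0.5.

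**Slack in the rounding.** 42/40 = 1.05. With design effect = 1 + (6 − 1) × ICC, this equals 1.05 at ICC = 0.05/5 = 0.01.

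**Design effect alone.** Effective N = 42/design effect. Power is from the noncentral t with noncentrality d × √(effective N) and effective N − 1 df.

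| ICC | Design effect | Effective N | True SE ÷ independence SE | Power, d=0.454 | Power, d=0.5 |
|---|---|---|---|---|---|
| 0.01 | 1.05 | 40.0 | 1.02 | 80% | 87% |
| 0.02 | 1.10 | 38.2 | 1.05 | 78% | 85% |
| 0.05 | 1.25 | 33.6 | 1.12 | 72% | 80% |
| 0.10 | 1.50 | 28.0 | 1.22 | 64% | 72% |

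The SE ratio is the square root of the design effect.

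**Type I error when groups are ignored.** I simulated 7 × 6 normal change scores with no true mean change and applied a one-sample t-test on 41 df at nominal 5%. Rejection rates are about 6%, 8% and 11% at ICC 0.02, 0.05 and 0.10.

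**Test with degrees of freedom from seven groups.** The same noncentrality with t on 7 − 1 = 6 df:

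| ICC | Power, d=0.454 | Power, d=0.5 |
|---|---|---|
| 0 | 69% | 77% |
| 0.02 | 65% | 73% |
| 0.05 | 60% | 68% |
| 0.10 | 52% | 60% |

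The ICC 0 row matters. Without any clustering, moving to 6 df already takes power at d=0.454 from 82% to 69%. Much of the loss in this table is therefore the price of the small number of groups, not of the correlation itself, and the two sets of figures should not be merged into one range.

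**The case against.** **The harm is conditional.** A reader might infer that the standard errors are certainly too small and that 80% power is certainly missed. The protocol does not support that. It gives no ICC of change; at ICC 0.01 the calibrated power is still 80%, and at 0.02 it is 78%. At d=0.5, power holds at 80% up to ICC 0.05 before any loss of degrees of freedom. This stands: the omission is certain, its size is not.

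**The earlier trial is thin evidence.** A reader might also infer that the protocol itself attributes that trial's failure to influence among group members. It reports the earlier investigators' speculation and calls it noteworthy. Section 2.4.1 names the implementation model as a major difference between the two interventions. Speculation about group discussion makes within-group correlation plausible but does not demonstrate it.

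**Some sources of between-group variation are limited.** Two facilitators (sections 4.5 and 4.10.1) and a single site (section 4.6) leave little room for facilitator or site differences. Section 4.9.1 allows retooling between iterations but does not say that it happens between these seven groups, and section 4.9.2 directs improvements to future studies. This stands too. It leaves group process as the main plausible source.

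**The simulation is a simplification.** It uses a one-sample t-test on normal change scores. The planned analysis is a three-time-point regression on an outcome that section 4.10.3 may log-transform or dichotomise. The type I figures are illustrative.

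**An analysis plan not shown here could add a group term.** That would repair the standard errors but not the N and power stated in section 4.4, which make no allowance for groups.

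**Conclusion.** The point holds in conditional form. Section 4.4 fixes subject-level random effects only and derives its sample size as if men were independent, while treatment is delivered wholly in interacting groups. Any positive ICC of change makes the standard error too small under that model, by a factor of 1.05 to 1.22 for ICC 0.02 to 0.10. Over the same range, power at N=42 is about 78% to 64% if the effect is the one that 40 independent men detect with 80% power, and about 85% to 72% if the standardised change is 0.5. Both series reflect the design effect alone.

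These figures rest on an assumed ICC, an assumed effect, a two-sided test and no dropout. That N=40 cannot be reproduced does not weaken the point, because any N derived under independence needs the same multiplier. For a Phase II study meant to supply an effect size, the main consequence is an interval that may be too narrow for planning the later trial.

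**What to change.** Add a group-level random effect on the time slope to the model in section 4.4, with degrees of freedom based on the seven groups. Group-clustered GEE with a small-sample correction is an alternative, not an equivalent: the two estimate different quantities if the endpoint is dichotomised, and both are fragile with seven clusters.

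Restate the power in section 4.4 for the test actually used and over a stated ICC range. Possible wording: *For the effect that 40 independent men would detect with 80% power, N=42 in 7 groups gives about 65%, 60% and 52% power at assumed ICCs of 0.02, 0.05 and 0.10 with t on 6 df; 6 df alone gives 69% at ICC 0.*

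If a group ICC is reported for planning the later trial, give it with its interval and read it cautiously. With seven groups of six, an observed ICC of 0.05 has a 95% interval of about −0.10 to 0.48 by the ANOVA F method.

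The cost is a change of wording and one more model term; group membership is known from how treatment is delivered. Confidence intervals widen and the stated power becomes less favourable. No extra participants are needed.
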